### 3. STUDY DESIGN

**Study design:** We aim to conduct a multicenter randomized non-inferiority trial comparing procedural sedation with general anesthesia in patients with symptomatic submucosal type 0 or I myomas up to 3 centimetres in diameter scheduled for hysteroscopic myomectomy. A cost-effectiveness study will be performed alongside the clinical study.

**Setting:** The proposed study will be performed within a consortium of university and teaching hospitals in the Netherlands. Patients will undergo hysteroscopic myomectomy either under general anesthesia or procedural sedation with propofol.

**Duration:** Preparation (6 months): protocol, database, approval medical-ethics committees. Inclusion (24 months): 205 patients. Follow-up (12 months): postoperative revision, recovery, complications. Analysis (6 months): data-analysis, publication.

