### **4.4 Sample size calculation**

The study is designed as a non-inferiority study, in which we want to investigate if hysteroscopic myomectomy under procedural sedation with propofol is non-inferior to the same surgical procedure under general anesthesia. With 205 women randomized we have 90% power to demonstrate non-inferiority, based on an estimated 2,5% incomplete resections in both groups, with an non-inferiority upper limit of 10% incomplete resections defined as non-inferior (i.e. a delta of 7.5%), an alpha of 0.025 and a drop-out rate of 10%.

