### **6.2 Randomisation, blinding and treatment allocation**

Randomisation will be performed web based through Alea with the use of a block design, with a variable block size. The expertise for this technology is already available for the study group (obs/gyn consortium). The study will not be double-blinded, as it is impossible to blind the health care workers and patients involved for the strategy to which the woman is allocated. The person performing the transvaginal ultrasonography at six weeks follow up, however, will be blinded for the study arm and judgement of completeness by the surgeon during the procedure. Patients will be able to complete the questionnaires online, through an link they receive by e-mail. In case patients wish to complete the questionnaires on paper, the research nurse will send the questionnaires by post at the follow-up moment.

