## 8. STATISTICAL ANALYSIS

### 8.1 Data analysis and presentation/synthesis

Primary analysis will be by intention-to-treat. We will also perform a per protocol analysis, given the non-inferiority design of the study, where crossover between the groups will increase the chances of concluding non-inferiority, if in reality the treatment is not-inferior. We will present the percentage of complete resections at 6 weeks in both groups, with according relative risks and 95% confidence interval. Differences will be tested with the chi-square test, or, if the expected cell count is low using the Fisher exact test. We will also calculate the relative risk, adjusted for center where the procedure has been performed. Complications during and after surgery, and re-interventions will be categorized and evaluated by a Clinical Evaluation Committee, independent and blinded for the type of surgery performed (where possible). Average pain intensity during the procedure as well as the highest pain intensity during the procedure will be reported as means with SD, risk differences between both groups will be calculated with according 95% confidence interval. Time to recovery and pain will be visualized in a graph, and analyzed using a mixed model, that can take into account repeated measures in the same woman over time. The quality of life and PBAC scores will be analyzed according the developed algorithms. We will perform a subgroup analysis for myoma size (<2 cm versus  $\geq 2$  cm) and for parity (nulliparous versus multiparous women).

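### The primary endpoint is analysed only by relative risks, crude and centre-adjusted, although the non-inferiority margin is an absolute 7.5-point difference

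*Protocol*

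**What the plan says.** **Margin (Protocol 4.4).** The sample size rests on a failure rate, "based on an estimated 2,5% incomplete resections in both groups", with an upper limit of 10% for the sedation arm. The limit is restated as an absolute difference: "i.e. a delta of 7.5%), an alpha of 0.025 and a drop-out rate of 10" per cent. The power claim is "With 205 women randomized we have 90% power to demonstrate non-inferiority".

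**Analysis (Protocol 8.1).** The primary endpoint is the percentage of complete resections at 6 weeks. It is to be shown by arm with relative risks and 95% confidence intervals, and tested by chi-square or, with low expected counts, Fisher's exact test. Centre then enters: "We will also calculate the relative risk, adjusted for center where the procedure has been performed". No estimator is named. The only risk difference in section 8.1 is attached to pain intensity, not to completeness of resection.

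**Randomisation (Protocol 6.2).** "Randomisation will be performed web based through Alea with the use of a block design, with a variable block size". No stratification factor is named.

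**Centres (Protocol 3).** "The proposed study will be performed within a consortium of university and teaching hospitals in the Netherlands". The number of centres is not given.

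**The concern.** A non-inferiority conclusion comes from setting one confidence limit against the margin, on the margin's own scale. Here the margin is a difference in percentage points, and every planned estimate for the primary endpoint is a ratio. Chi-square and Fisher tests address a null hypothesis of no difference, and a non-significant result there does not show that sedation is at most 7.5 points worse.

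Without a stated conversion, whoever writes the report must choose after the fact which ratio to use (complete or incomplete resection), what ratio margin to apply, or whether to compute a difference that the protocol did not plan. These choices can give different answers from the same data. The centre-adjusted analysis inherits the problem, and section 6.2 does not say whether allocation was balanced on the factor being adjusted for.

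**Working it through.** **Inputs.** From Protocol 4.4: 2.5% incomplete in both arms, margin 7.5 points, alpha 0.025, power 90%, drop-out 10%, 205 randomised. Assumed: 1:1 allocation and one-sided alpha, since neither is stated and together they reproduce the sample size; and 5, 10 or 15 centres, since the number is not given.

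**1. The plan's own sample size.** The formula is on the risk-difference scale:

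n per arm = (1.960 + 1.282)² × 2 × 0.025 × 0.975 / 0.075² = 10.507 × 0.04875 / 0.005625 = 91.06, so 92 per arm and 184 evaluable. Then 184 / 0.90 = 204.4, so 205. The stated figure reproduces, so the power claim belongs to a risk-difference analysis.

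**2. The margin as a ratio.** With control failure rate p, the 7.5-point margin equals (p + 0.075)/p for incomplete resection and (1 − p − 0.075)/(1 − p) for complete resection.

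| Control rate p | Ratio, incomplete | Ratio, complete |
|---|---|---|
| 1% (assumed) | 8.5 | 0.924 |
| 2.5% (plan) | 4.0 | 0.923 |
| 5% (assumed) | 2.5 | 0.921 |

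The equivalent shifts greatly for incomplete resection and little for complete resection. The protocol states neither.

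**3. The same expected data on three scales.** Take 92 per arm, 2.5% incomplete in each arm and large-sample 95% limits.

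- Risk difference: half-width 1.96 × √(2 × 0.025 × 0.975/92) = 4.5 points. Upper limit 4.5, below 7.5.
- Relative risk of complete resection: SE(log) = √(2 × (0.025/0.975)/92) = 0.0236. Limits 0.955 to 1.047; the lower limit is above 0.923.
- Relative risk of incomplete resection: SE(log) = √(2 × (0.975/0.025)/92) = 0.921. Limits 0.16 to 6.1; the upper limit is above 4.0.

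The first two would support non-inferiority. The third would not.

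**4. Can the centre-adjusted relative risk be estimated?** Expected incomplete resections are 184 × 0.025 = 4.6, and expected complete resections 184 − 4.6 = 179.4.

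- *Complete resections.* In simulated trials of 184 women, with 5 to 15 centres of equal expected size, Mantel-Haenszel and robust Poisson estimates existed in every run. The median 95% interval was about 0.96 to 1.04, and Mantel-Haenszel coverage was 95 to 97%.
- *Incomplete resections.* P(at least one arm with no event) = 1 − (1 − 0.975⁹²)² = 1 − (1 − 0.0974)² = 18.5%. Expected centres with no event, K × 0.975^(184/K), are 2.0 of 5, 6.3 of 10 and 11.0 of 15. The Mantel-Haenszel ratio was estimable and non-zero in about 81 to 82% of runs, with a median upper-to-lower limit ratio of about 49 to 55. A log-binomial model with fixed centre effects fitted without separation in about 8% of runs with 5 centres and 0% with 10.

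**5. Balance within centres.** For an assumed 20-woman centre, a split of 13:7 (65:35) or worse has probability P(|X − 10| ≥ 3) = 0.263 under simple allocation, X ~ Binomial(20, 0.5). Under central blocks not stratified by centre (sizes 4 and 6 assumed), simulation gave about 24%.

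**The case against.** **The relative risk is of complete resections, so sparse events are not a problem.** This stands. A reader might infer from the 4.6 expected failures that the centre-adjusted relative risk will fail to converge or rest on a few centres. The documents do not support that. Sections 6.1.1 and 8.1 both name complete resection as the outcome, and on it standard estimators work. The instability applies only if the ratio is taken on incomplete resections, the outcome used for sizing in section 4.4.

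**On complete resections the ratio equivalent hardly moves, 0.921 to 0.924, so the relative risk could be read against it.** Arithmetically this is true, and it limits the damage. But the protocol gives no ratio margin, and a margin chosen after the data are seen is not prespecified.

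**The adjusted relative risk is supplementary, and its estimator belongs in the statistical analysis plan.** Both points are fair. The absence of a named estimator is not held against the protocol. The effect scale is different: section 8.1 chooses it, and it does not match section 4.4. The mismatch affects the crude primary analysis first and the adjusted one equally.

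**Section 6.2 is silent on stratification; it does not say that there is none.** This is correct, so it is a point to clarify. A reader might also infer that unstratified blocks confound arm with centre and bias the result. They do not: randomisation still protects the comparison, and adjusting for an unstratified factor is valid. What is lost is balance and some precision in small centres.

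**Conclusion.** The mismatch is real and lies in stated text. The margin and the sample size are absolute, the planned estimates are ratios, and the planned tests are of difference, so section 8.1 contains no analysis that tests the stated margin directly. The choice of scale matters: with the trial's own expected data, the risk difference passes (4.5 against 7.5 points) while the ratio of incomplete resection fails (6.1 against 4.0). On complete resection the ratio would lead to the same conclusion as the difference, but only against a margin that the protocol does not give.

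These results assume 1:1 allocation, 184 evaluable women, the planned 2.5% rate and large-sample intervals, which are approximate with so few failures. The simulation and zero-event figures for centres also depend on the assumed 5 to 15 centres.

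This should be changed before analysis. The stratification point is secondary: a chance of about 24 to 26% of a marked split in a 20-woman centre is a matter of precision, not bias.

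**What to change.** In section 8.1, replace the centre-adjusted relative risk with a centre-stratified Mantel-Haenszel risk difference in incomplete resections (sedation minus general anaesthesia) and its 95% confidence interval. Conclude non-inferiority if the upper limit is below 7.5 percentage points. This matches section 4.4, gives the same conclusion whether the outcome is coded as complete or incomplete, and keeps centres without events provided both arms are present. State that very small centres will be pooled by a rule set in advance, and name a sparse-data variance or interval method for few or no events; at the planned rate, the chance of no failure in either arm is 0.975¹⁸⁴ = 0.9%. Relative risks may stay as description.

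In section 6.2, name centre as a stratification factor in the web randomisation, or state that it already is one. If recruitment has begun without it, say so; the adjusted analysis remains valid.

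The cost is a few sentences in section 8.1 and one randomisation setting, with no extra patients or data.

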## **5. TREATMENT OF SUBJECTS**

### **5.1 Investigational product/treatment**

#### **Procedural sedation and analgesia in an outpatient setting**

According to guidelines from the Health Care Inspectorate (IGZ) and Dutch Institute for Healthcare Improvement (CBO) non-anesthesiologist administered Propofol (NAAP) sedation is given and monitored by a qualified sedation practitioner [30-31]. The patient will be assessed by the sedation practitioner immediately prior to surgery on the basis of a pre-operative questionnaire. Non-invasive blood pressure, electrocardiogram and oxygen saturation are measured before vascular access is obtained. Propofol and alfentanil are used for procedural sedation.

Hysteroscopic resection is performed by an experienced surgeon by standard procedure in an office-based setting. Patients are observed after the procedure by qualified personnel and discharged as soon as all the discharge criteria are met, normally within 1 to 1.5 hours.

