#### **General anesthesia**

General anesthesia can be volatile based or total intravenously, with the use of a laryngeal mask. Postoperatively, patients will be observed in the recovery room and discharged home from the clinic when all the discharge criteria are met.

The way hysteroscopic resection is performed under general anesthesia does not differ from the way it is performed under procedural sedation.

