### **Characteristics registered during the procedure**

- completeness of resection as judged by surgeon
- surgical complications
- anesthesiologic complications (desaturation, airway obstruction, dysrhythmias, blood pressure drops, ECG alterations)
- operating time
- intravasation/fluid deficit
- recovery time (time from end of procedure until completely awake and communicative)
- use of pain medication and dose
- pain intensity measured by VAS scores
- duration of hospitalization (hours)

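### Pain during the procedure is to be compared between arms by a risk difference, but no pain risk is defined and the protocol gives the general-anesthesia arm no way to rate it

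*Protocol*

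**What the plan says.** Protocol section 8.1 names two pain variables, "Average pain intensity during the procedure as well as the highest pain intensity during the procedure". It then says that average and "highest pain intensity during the procedure will be reported as means with SD, risk differences between both groups will be calculated", with a 95% confidence interval. The next sentence adds a second pain analysis: "Time to recovery and pain will be visualized in a graph, and analyzed using a mixed model", to allow for repeated measures in the same woman. It does not say which pain time points enter that model.

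On measurement, section 6.3 (characteristics registered during the procedure) lists "pain intensity measured by VAS scores". Pain by VAS also appears in the section 6.3 list of characteristics registered after the procedure, and in the questionnaire table at 24 hours.

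On the state of the women during surgery, section 5.1 says for the control arm: "General anesthesia can be volatile based or total intravenously, with the use of a laryngeal mask". For the experimental arm it says: "Propofol and alfentanil are used for procedural sedation".

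Pain is a secondary outcome (sections 2 and 6.1.2).

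**The concern.** Two features of the section 8.1 sentence do not fit the data it describes.

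The first is the effect measure. A risk difference is a difference between two proportions and needs a yes/no outcome. The sentence applies it to a score summarised by mean and SD.

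The second is the moment of measurement. Both pain variables refer to the time during the procedure, and the contrast is between both groups, yet one group is under general anesthesia at that time. If the sentence is followed literally, the pain contrast is either undefined or reflects unconsciousness in one arm and not a difference in pain experienced. Leaving the effect measure uncorrected also leaves room for a pain cut-off to be chosen once data are in hand, in a trial where patients and care staff know the allocation (section 6.2).

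**Working it through.** The protocol gives no figure for the pain comparison (no expected mean, SD or difference), so the check sets its statements side by side.

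**Step 1: is there a risk to difference?**
- Scale: a VAS score (section 6.3).
- Summary: mean and SD (section 8.1).
- Binary pain event, responder definition or cut-off: none in the endpoint, procedure or analysis sections.

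A risk difference is p(sedation) − p(general anesthesia), where each p is the number of women with the event divided by the number of women. With no event defined, neither p exists. The contrast that goes with means and SDs is mean(sedation) − mean(general anesthesia), with its 95% CI.

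**Step 2: can both arms supply the score?**
- Control arm during surgery: general anesthesia with a laryngeal mask (section 5.1).
- When the protocol expects a woman to be able to communicate: it defines "recovery time (time from end of procedure until completely awake and communicative", so it counts this from the end of surgery onwards.
- Rule for obtaining a VAS during surgery under general anesthesia, or for confining the comparison to one arm: none.

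That control women cannot rate pain during surgery is an inference from these statements, since the protocol does not say it outright. The inference is a short one. The difference in means in step 1 then has no valid second term when the variable is pain during the procedure.

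**Step 3: how many women?** Section 4.4 plans 205 randomised. Section 6.2 does not state the allocation ratio. If it is 1:1, the control arm has 205 / 2 = 102.5, or about half of the women.

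**Step 4: what does the protocol collect that both arms can rate?** VAS pain after the procedure and at 24 hours (both section 6.3). At these times women in either arm can give a score, and section 8.1 already has a mixed model for pain that could use them.

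**Step 5: does the point reach the primary design?** Inputs from section 4.4: 2.5% incomplete resections in both arms, delta 7.5 percentage points, one-sided alpha 0.025, power 90%, drop-out 10%; 1:1 allocation is assumed. By the usual normal approximation,

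n per arm = 2 × 0.025 × 0.975 × (1.960 + 1.282)² / 0.075² ≈ 91.1, rounded up to 92.

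The total is 184, and 184 / 0.9 = 204.4, rounded up to 205. The stated figure is reproduced and uses no pain input, so it is unaffected.

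**The case against.** The strongest reply has four parts.

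*The effect measure is probably a slip.* Means with SD and a confidence interval make it likely that a difference in means was intended, and an analysis plan would normally name it. This is fair as to intent. The sentence still names a quantity that cannot be formed from the data described, and it should be corrected.

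*The score may be recalled afterwards.* The section 6.3 list is loosely headed: it also contains recovery time and duration of hospitalization, which cannot be recorded during surgery. A recalled score is possible, but the protocol does not say so, and section 8.1 refers to the time during the procedure for both variables. Recall would not supply the missing control data either, because a woman under general anesthesia has no experience of surgery to average or to take a peak from.

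*The sedation arm may be limited too.* Women receiving propofol and alfentanil may not be able to rate pain reliably during the procedure, and the protocol does not show that they can. This stands. It is why the remedy should not presume valid scores throughout the sedation arm.

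*A usable pain comparison is largely in place.* A reader might infer that the trial has no valid between-arm pain analysis. The protocol does not support that, because section 8.1 also plans a mixed model for pain and post-procedural VAS is collected. What is missing is a statement that those scores are the ones compared.

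A reader might also infer that a repeated-measures model is wrong for time to recovery, because recovery time is one duration per woman. The protocol does not settle this. The phrase may refer to the Recovery Index (RI-10), which is collected at 24 hours, 2 weeks and 8 weeks, and repeated scores of that kind suit such a model. No change to the recovery analysis is asked for here.

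**Conclusion.** The point holds for one sentence of section 8.1 and on two counts. The risk difference is undefined for a VAS score with no pain event specified. The between-arm contrast on pain during the procedure has no valid control data, because the protocol puts that arm under general anesthesia and describes no way of rating pain there.

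The size is limited. It concerns one of eight listed secondary outcomes, and one of two planned analyses of it. The share of women without valid intra-procedural scores is about half only if allocation is 1:1, which is an assumption. One might argue that the control scores would be entered as zero, so that the difference would simply equal the sedation-arm mean. That is arithmetically true, but hypothetical: nothing in the protocol suggests zeros would be entered. The primary endpoint and the sample size of 205 are untouched. The change should be made, but it is not critical to the trial's main conclusion.

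**What to change.** In section 8.1:

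1. Replace the risk difference for pain with a difference in means and its 95% CI.
2. State that the between-arm pain comparison uses the VAS collected after the procedure and at 24 hours, and name these as the time points of the pain mixed model already planned. The after-procedure list gives no clock time, so one should be stated. If that score and the 24-hour score prove to be the same measurement, a single difference in means is enough.
3. Report average and highest VAS during the procedure descriptively only, without a between-arm test, in women able to rate it. State when and how the rating is made (at the time or recalled, by whom it is asked) and how many women supplied it.

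The cost is small. The change is to wording, and the VAS scores it relies on are already collected. The one loss is that the trial will give no between-arm estimate of pain during the procedure, which the present plan could not validly provide either.

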### **Questionnaires**

Participating women will fill in questionnaires at baseline, which will be given before the surgical procedure. During follow-up, patients will fill in questionnaires at 24 hours, 2 weeks, 8 weeks, 6 and 12 months after randomisation. Questionnaires will contain:

- Short questionnaire on side effects 24 hours after surgery.
- the EuroQoL (EQ-5D-5L) questionnaire (15 questions) to assess the quality of life
- PBAC scores to assess the amount of menstrual blood loss
- Uterine Fibroid Symptoms – Quality of Life (UFS-QoL) questionnaire (37 questions) to assess the quality of life focussing on patients suffering from uterine fibroids
- Recovery Index (RI-10) questionnaire (10 questions): to assess the patients' recovery process

- Medical Consumption Questionnaire (iMCQ)[32]: for cost effectiveness analysis
- Productivity Cost Questionnaire (iPCQ)[33] to assess productivity loss
- Short questionnaire on recurrence and re-interventions at 12 months after surgery.

|           | Side effects
Pain
(VAS) | EQ-5D-5L | PBAC | UFS-QoL | RI-10 | iMCQ | iPCQ | Re-intervention |
|-----------|-------------------------------|----------|------|---------|-------|------|------|-----------------|
| Baseline  |                               | X        | X    | X       |       |      |      |                 |
| 24 hours  | X                             | X        |      |         | X     |      |      |                 |
| 2 weeks   |                               | X        |      |         | X     |      |      |                 |
| 8 weeks   |                               | X        | X    | X       | X     | X    | X    |                 |
| 6 months  |                               |          |      |         |       | X    |      |                 |
| 12 months |                               | X        | X    | X       |       | X    |      | X               |

A patient preference study (for which a different study protocol will be created) will be conducted alongside the trial including evaluation of patient satisfaction.

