## PATIENT OUTCOME ANALYSIS CEA

Societal costs will be related to the following effect measures in the economic evaluation:

- 1) % of complete resection;
- 2) quality-adjusted life-years (QALYs) based on the Dutch tariff for the EuroQol (EQ-5D-5L) [36-37].

The analysis will be done according to the intention-to-treat principle. Missing cost and effect data will be imputed using multiple imputation. Incremental cost-effectiveness ratios (ICERs) will be calculated by dividing the difference in mean total costs between the treatment groups by the difference in mean effects. Bootstrapping with 5000 replications will be used to estimate 95% confidence intervals around cost differences and the uncertainty surrounding the ICERs. Uncertainty surrounding the ICERs will be graphically presented on cost-effectiveness planes. Cost-effectiveness acceptability curves showing the probability that the intervention is cost-effective in comparison with usual care for a range of different ceiling ratios will also be estimated [38]. Adjustment for confounders and effect modifiers will be done if necessary.

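### The incremental QALY in Section 8.2 is an unadjusted difference in means, with adjustment left to an undefined later judgement, although baseline EQ-5D-5L is collected

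*Protocol*

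**What the plan says.** Section 8.2 of the protocol (patient outcome analysis) relates societal costs to two effects: the percentage of complete resections, and QALYs from the EQ-5D-5L with the Dutch tariff. The ratio is the difference in mean total costs over the difference in mean effects, with multiple imputation for missing data and 5000 bootstrap replications. The only sentence on covariates is "Adjustment for confounders and effect modifiers will be done if necessary".

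Section 6.3 (Questionnaires) provides the baseline data: "Participating women will fill in questionnaires at baseline, which will be given before the surgical procedure". Its table marks EQ-5D-5L, PBAC and UFS-QoL at baseline. EQ-5D-5L is repeated at 24 hours, 2 weeks, 8 weeks and 12 months; PBAC and UFS-QoL are repeated at 8 weeks and 12 months.

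For the clinical comparison of these scores, Section 8.1 says "The quality of life and PBAC scores will be analyzed according the developed algorithms". By contrast, time to recovery and pain are to be "analyzed using a mixed model, that can take into account repeated measures in the same woman over time". Centre is the only covariate that Section 8.1 names, and it is for the relative risk of the primary outcome.

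**The concern.** Section 8.2 states an estimator as well as an option. The estimator is an unadjusted difference in means. The option to adjust depends on need, and need is not defined. In a randomised trial, baseline differences between arms arise by chance, so without a stated rule need can only be judged by looking at the data. Whoever does the analysis can then choose between an adjusted and an unadjusted incremental QALY with both in view.

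The choice matters because the incremental QALY is the denominator of a ratio. Section 9.3 expects the two strategies to be equally effective. Section 1 expects some gain in quality of life but gives no size. If the true QALY difference is small, a modest chance imbalance can change the ratio and the acceptability curve noticeably. Section 6.2 describes the allocation as follows: "Randomisation will be performed web based through Alea with the use of a block design, with a variable block size". It names no stratification factor, so the design does not restrain imbalance in baseline utility.

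**Working it through.** **The plan's own figure.** Section 4.4 states: "With 205 women randomized we have 90% power to demonstrate non-inferiority", "based on an estimated 2,5% incomplete resections in both groups", a margin of 7.5 points, alpha 0.025 and 10% drop-out. With 1:1 allocation (assumed), one-sided alpha and unpooled variance:

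- n per arm = (1.960 + 1.282)² × 2 × 0.025 × 0.975 / 0.075² = 91.1, so 92 per arm and 184 in total.
- 184 / 0.9 = 204.4, so 205.

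The stated 205 is reproduced. The working below uses 92 women per arm.

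**Assumptions, not in the protocol.** Utility SD 0.20, equal at each time; correlation r of 0.3 to 0.7 between baseline and follow-up; QALY as a trapezoidal area under the curve; baseline taken close to the procedure.

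**Step 1: size of a chance imbalance.**
- SE = SD × √(2/92) = 0.147 SD.
- 95% of trials fall within 1.96 × 0.147 = ±0.29 SD.
- At SD 0.20, one SE is 0.147 × 0.20 = 0.029.

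**Step 2: where an area-under-the-curve QALY gets its weight.** Days 0, 1, 14, 56 and 365 give these trapezoid weights:

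| Time | Calculation | Weight |
|---|---|---|
| Baseline | (1/2)/365 | 0.0014 |
| 24 hours | (14/2)/365 | 0.019 |
| 2 weeks | (55/2)/365 | 0.075 |
| 8 weeks | (351/2)/365 | 0.481 |
| 12 months | (309/2)/365 | 0.423 |

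Baseline has a direct weight of about 0.14%. The 8-week and 12-month scores carry 0.481 + 0.423 = 90%. Imbalance therefore acts almost wholly through the correlation of baseline with those two scores.

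**Step 3: shift in the QALY difference at a one-SE imbalance.** With equal SDs, a share r of the imbalance is expected to persist at follow-up. Counting only the 8-week and 12-month points, the shift is 0.029 × 0.904 × r. Counting all points, with the same r at each follow-up, it is 0.029 × [0.0014 + 0.9986 × r]. (The unrounded imbalance, 0.0295, is used.)

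| r | 8 weeks and 12 months only | All points |
|---|---|---|
| 0.3 | 0.008 | 0.009 |
| 0.5 | 0.013 | 0.015 |
| 0.7 | 0.019 | 0.021 |

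The range is about 0.008 to 0.02. It scales with the assumed SD: half the SD gives half the shift.

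**Step 4: precision.** The variance of a baseline-adjusted difference, relative to an unadjusted follow-up difference, is 1 − r². The detectable difference is for 80% power at two-sided 0.05; without adjustment it is (1.960 + 0.842) × 0.147 = 0.41 SD.

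| r | Variance cut (r²) | CI narrower by, 1 − √(1 − r²) | Detectable difference |
|---|---|---|---|
| 0.3 | 9% | 5% | 0.39 SD |
| 0.5 | 25% | 13% | 0.36 SD |
| 0.7 | 49% | 29% | 0.295 SD |

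These figures are for a single follow-up score. For the QALY itself, r is the correlation of baseline utility with the QALY.

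**The case against.** The strongest reply is that the model for secondary questionnaire scores is commonly left to a statistical analysis plan, and one may exist. That stands for Section 8.1. A reader might infer from its wording that the baseline scores are collected and then not used. The protocol does not say so: its sentence on algorithms excludes neither change scores nor baseline covariates. Baseline EQ-5D-5L would normally be the first point of the QALY curve and may enter the imputation model. Neither use adjusts the comparison between arms, however, and Section 8.2 is not silent: it states the unadjusted estimator and a conditional rule.

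A reader might also infer that baseline imbalance passes straight into the QALY. On the protocol's schedule it does not. The direct weight is about 0.14%, so an imbalance of 0.029 would contribute only about 0.00004 QALY by that route (0.029 × 0.0014). For the same reason, starting the curve at baseline does not replace adjustment. A shift as large as the whole imbalance would need full persistence to 12 months, which cannot be presumed after surgery meant to change symptoms.

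It is also fair to say that randomisation keeps the unadjusted difference unbiased and that its confidence interval already allows for chance imbalance. Both points stand. What remains is lost precision, and an interval whose meaning weakens if the choice to adjust follows the data. Nor can it be claimed that imbalance would exceed any effect of the type of anaesthesia, because the protocol gives no expected QALY difference.

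**Conclusion.** The point holds for Section 8.2. The incremental QALY is defined without adjustment, and the escape clause has no criterion and no covariate, while the obvious covariate is already on the questionnaire schedule. A one-SE imbalance would move the QALY difference by about 0.008 to 0.02, and adjustment would cut the variance of a follow-up score by 9% to 49%. Both ranges depend on the assumed correlations of 0.3 to 0.7, and the first also on the assumed SD and QALY method. At the low end the gain is small; at the high end it is material.

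For Section 8.1 the point is only a recommendation to settle the role of baseline when the comparison is specified. This concerns efficiency and prespecification in the secondary and economic outcomes. The primary endpoint has no baseline value, the ratio per complete resection has no baseline utility in its denominator, and the sample size of 205 is unchanged.

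**What to change.** In Section 8.2, replace the sentence on conditional adjustment. The new text should make the main cost-utility estimate a regression of QALYs on treatment arm and baseline EQ-5D-5L utility, run within the multiple imputation and the bootstrap. The unadjusted difference should be reported as a sensitivity analysis. Merely deleting the condition would not do, because it would leave an unqualified promise to adjust for unnamed variables.

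In Section 8.1, or in the analysis plan, state that any between-arm comparison of EQ-5D-5L, UFS-QoL and PBAC includes that outcome's own baseline score as a covariate. Any transformation of PBAC should be fixed beforehand and not chosen from the observed distribution.

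The cost is wording and a little programming. No data beyond those already scheduled and no additional women are needed; missing baseline utilities can be handled in the imputation already planned.
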